### Objective

Our specific aims are (1) to study the effects of COVID-19 on maternal and obstetric morbidity and mortality, including those of indicators such as preeclampsia, abortion, fetal malformation, fetal growth, and premature birth; (2) to investigate the presence of SARS-CoV-2 and anti–SARS-CoV-2 antibodies in the cerebrospinal fluid (CSF) of women with symptomatic COVID-19 undergoing spinal anesthesia for a cesarean section; (3) to determine the serum proinflammatory and regulatory cytokine profiles of pregnant women with symptomatic COVID-19; (4) to determine the CSF proinflammatory and regulatory cytokine profiles of pregnant women with symptomatic COVID-19 undergoing spinal anesthesia for a cesarean section; (5) to study the histopathological markers of inflammatory and thrombotic phenomena in the placenta; (6) to study the correlations between the aforementioned serum and histologic biomarkers of COVID-19 and the outcomes of pregnancy, delivery, puerperium, and childbirth as well as the correlations between biomarkers and short- and long-term health outcomes during infancy; (7) to study the association between the use of maternal pharmacological therapy for treating COVID-19 and offsprings’ health outcomes; (8) to evaluate the effects of COVID-19 exposure during different stages of pregnancy on fetal, neonatal, and infantile morbidity and mortality; and (9) to evaluate the effects of in-pregnancy COVID-19 exposure on children’s somatic and neurological development and energy metabolism from birth up to 5 years of age.

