**Figure 1 figure1:**
[figure not shown]
Pregnancy Outcomes and Child Development Effects of SARS-CoV-2 Infection Study follow-up flowchart.

The PREGNANT substudy will follow—until day 21 postpartum—pregnant women who are exposed to SARS-CoV-2 at any phase of gestation and compare them to a control group consisting of nonexposed pregnant women. The BORN substudy will follow the children of the women included in the preceding (PREGNANT) branch. These children will be allocated into two comparison groups (exposed and nonexposed) according to their mothers’ in-pregnancy exposure status and will be followed up by a multidisciplinary team of health professionals from birth up to the age of 5 years. This team will conduct regular consultations every month up until the children reach 6 months of age, every 3 months up until the children reach 2 years of age, and every 6 months up until the children reach 5 years of age. Mothers and children may attend nonscheduled visits, as needed, for clinical reasons as well as specific appointments for conducting the procedures and tests described in this protocol.

The PROUDEST will be conducted from July 2020 to December 2026 in Brasília, Brazil. The recruitment of pregnant and newborn dyads will be carried out by using data from the Epidemiological Surveillance Center of the Federal District. These mother-fetus dyads will be followed up to childbirth (and puerperium in the case of mothers) until December 2021, which is when the last included dyads are expected to undergo childbirth in two different hospitals—the University Hospital of Brasília and Asa Norte Regional Hospital (the reference public medical center for COVID-19 in the Federal District in Brazil). Both hospitals are located in central urban areas and are included in the Brazilian public health system (Sistema Único de Saúde), which primarily serves the low-income population. Thus, the results of the PREGNANT substudy will be published as soon as the analyses are completed. The children will be followed from childbirth up to December 2026, which is when the last admitted neonate will turn 5 years old. As the BORN substudy is lengthy, partial results may be disclosed during the course of the study, but the final data set will be made available in the second half of 2026.

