Pregnant women included in the study must be aged >18 years. COVID-19 exposure will be defined as a first-time RT-PCR test, serology test, or rapid test that returns positive results during pregnancy and is confirmed by a second test. Nonexposure to COVID-19 will be defined as asymptomatic pregnant women with negative serology tests (immunoglobulin G [IgG] and immunoglobulin M [IgM] tests), which will be conducted at 14-21 days postpartum.

Pregnant women with preexisting chronic diseases (except diabetes and hypertension); those taking continuous medications; those who consume tobacco, alcohol, or other drugs; and those with other suspected or confirmed congenital infections will be excluded.

Neonates whose mothers qualified for inclusion in the PREGNANT substudy (had these women been screened) may also be admitted to the BORN substudy, even if their mothers did not participate in the preceding branch.

Children initially assigned to the control (nonexposed) group who later become infected with SARS-CoV-2 (as confirmed via laboratory tests) during follow-up will be excluded from all analyses (from the time of SARS-CoV-2 infection diagnosis onward). However, they will continue to receive assistance under the same standards until the end of the study.

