### Sample Size Calculation

No precise data are available on the prevalence of SARS-CoV-2 infection among pregnant women in Brazil, but international reports have estimated that up to 15.3% of all pregnancies have been exposed to the virus [38]. Recent data have indicated a birth rate of 44,195 newborns per year in the Federal District [39]. Thus, after considering an “infinite” population (>20,000 pregnant women), assuming a 15% prevalence of SARS-CoV-2–exposed pregnancies, and accounting for a confidence level of 95% and a margin of error of 5%, the minimum sample size for a random sample of SARS-CoV-2–exposed women would be 195. This calculation expectedly yielded a similar number for a random sample of SARS-CoV-2–exposed children. If we set the expected dropout rate for the BORN substudy to 20%, the required number of SARS-CoV-2–exposed mothers (those giving birth to the BORN participants) would increase to 234.

Our sampling approach however is not truly random; it is based on convenience, as eligible subjects will present to the recruitment centers. The aforementioned calculations only serve as a reference for avoiding the overestimation of the inclusion of participants. Given the limited amount of available knowledge regarding the effects of SARS-CoV-2 infection on pregnancy and child development, which resulted in the eminently exploratory character of our study, we adopted an “as much as feasible, but no more than reasonable” approach for defining the sample size.

We set an a priori number of 300 SARS-CoV-2–exposed women for the PREGNANT phase. This will result in the inclusion of the expected 300 SARS-CoV-2–exposed children in the BORN phase. The subject allocation rate between the exposed and control groups was 1:1. This indicated the need for an additional 300 mothers and 300 children to constitute the nonexposed control groups. Hence, the overall sample size of the PROUDEST was set to 1200 participants (600 mother-child dyads consisting of 300 SARS-CoV-2–exposed mother-child dyads and 300 control dyads).

To promote participant retention and completed follow-ups at pregnancy and pediatric outpatient clinics, we will actively search for patients via phone and email.

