### Statistical Analysis

All data will be stored in REDCap (Research Electronic Data Capture; Vanderbilt University), which is a tool for building and managing web-based surveys and databases. All variables will be summarized via standard descriptive techniques according to their type and distribution. For the bivariate analysis, differences in categorical variables between the exposed and unexposed groups will be verified with the Chi-square test or Fisher exact test, whereas differences in continuous variables between the groups will be assessed with the Student *t* test or the Mann-Whitney U test.

For dichotomous outcomes, binomial regression models, which will be adjusted based on the unbalanced and relevant background features of the comparison groups, will be used to estimate the relative risks between the exposed and nonexposed groups. Partial correlation and general linear models will be used to assess the associations between continuous outcome variables and covariates; adjustments for imbalances will be made as appropriate. A *P* value of <.05 will be considered significant. The control group will be composed of nonexposed mother-child dyads that meet the inclusion criteria. However, those with positive serology tests (IgG and IgM tests conducted at 14-21 days postpartum) will not be included in the control group. The groups will not be matched or paired based on age or other variables. However, any differences between the groups will be adjusted later via statistical means.

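### The control group for the PREGNANT comparison is defined in conflicting ways, and applying the Statistical Analysis wording literally could leave out control pregnancies that end in abortion or fetal death

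*Protocol article*

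**What the plan says.** All references are to the protocol article.

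- **Outcomes.** Aim 1 in the Objective section covers maternal and obstetric morbidity and mortality, "including those of indicators such as preeclampsia, abortion, fetal malformation, fetal growth, and premature birth". Aim 8 adds fetal mortality by stage of exposure.
- **Effect measure.** For dichotomous outcomes, the Statistical Analysis section plans binomial regression to estimate relative risks between exposed and nonexposed groups.
- **Controls in the analysis.** The same section states: "The control group will be composed of nonexposed mother-child dyads that meet the inclusion criteria". It adds that those with positive IgG and IgM serology at 14-21 days postpartum are left out of the control group.
- **Controls in the design.** The Study Design text after Figure 1 says that PREGNANT will follow women exposed at any phase of gestation and "compare them to a control group consisting of nonexposed pregnant women".
- **Timing of group status.** Study Design defines exposure as "a first-time RT-PCR test, serology test, or rapid test that returns positive results during pregnancy and is confirmed by a second test". Nonexposure requires an asymptomatic woman with negative serology at 14-21 days postpartum.
- **Sample size.** The Sample Size Calculation section states: "We set an a priori number of 300 SARS-CoV-2–exposed women for the PREGNANT phase". It continues: "This will result in the inclusion of the expected 300 SARS-CoV-2–exposed children in the BORN phase". The total is then given as "600 mother-child dyads consisting of 300 SARS-CoV-2–exposed mother-child dyads and 300 control dyads".

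**The concern.** A pregnancy that ends in abortion or fetal death leaves no child, so in the ordinary sense it is not a mother-child dyad. If the control group consists of such dyads, a nonexposed woman who loses her pregnancy has no clear place in the numerator or the denominator. An exposed woman with the same outcome qualifies through a test in pregnancy and can be counted.

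The serology rule pulls the same way. Exposed status is settled during pregnancy, whereas control status waits for a test 14-21 days postpartum. The article does not say whether that window applies after an early loss, or what happens to a nonexposed woman who is not tested then.

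At stake is whether the relative risks for abortion and fetal death can be estimated and, if they can, whether a difference reflects infection or only the way controls were admitted.

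**Working it through.** **Step 1. The plan's own count.** The sample size section has 300 exposed women and 300 exposed children, and as many controls: 300 + 300 + 300 + 300 = 1200 participants, or 600 dyads. This pairs one child with each woman in both groups. The plan gives no pregnancy-loss risk and no target relative risk for any loss outcome, so there is no planned figure for this comparison to reproduce.

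**Step 2. The definitions side by side.**

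| Section | Exposed | Control |
|---|---|---|
| Study Design | Women, test positive in pregnancy | Pregnant women; nonexposure confirmed 14-21 days postpartum |
| Sample Size Calculation | 300 women, then 300 dyads | 300 mothers and 300 children, then 300 dyads |
| Statistical Analysis | Not separately defined | Mother-child dyads, excluding those seropositive 14-21 days postpartum |

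The word dyad is itself unsettled. Study Design says: "The recruitment of pregnant and newborn dyads will be carried out by using data from the Epidemiological Surveillance Center". It then uses the term for mother and fetus before birth, which would include pregnancies later lost. The Statistical Analysis section uses it for mother and child.

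**Step 3. What each reading implies for the relative risk of loss.**

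- *Pregnant women in both groups, every loss counted:* no bias from this source.
- *Live-birth dyads in both groups:* no losses in either group, so the ratio is 0/0 and undefined. It is not raised.
- *Women in the exposed group, controls admitted only in part after a loss:* biased upward.
- *Women in the exposed group, no control loss admitted:* zero control events, so no finite relative risk.

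**Step 4. Size under partial omission.** Let r be the true loss risk, equal in both groups (true relative risk 1), and f the share of control losses that can enter the control group. All exposed losses are counted. Then

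- observed control risk = f·r / (f·r + 1 − r)
- observed relative risk = r divided by that = (1 − r(1 − f)) / f

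Neither r nor f is in the documents. Both are assumed.

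| r | f = 1 | f = 0.75 | f = 0.5 | f = 0.25 |
|---|---|---|---|---|
| 2% | 1.00 | 1.33 | 1.98 | 3.94 |
| 5% | 1.00 | 1.32 | 1.95 | 3.85 |
| 10% | 1.00 | 1.30 | 1.90 | 3.70 |
| 15% | 1.00 | 1.28 | 1.85 | 3.55 |

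Example for r = 5%, f = 0.5: control risk = 0.025 / (0.025 + 0.95) = 0.0256, and 0.05 / 0.0256 = 1.95. Per 300 women this is 15 exposed losses against 7.7 control losses.

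The distortion depends mainly on f and little on r. What matters is therefore how control losses are classified, and that is what the article leaves contradictory.

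**The case against.** The strongest reply is that Study Design already defines the PREGNANT controls as pregnant women, in the same sentence that describes the exposed. The sample size section counts both groups alike, and dyad also covers mother and fetus. On this view the sentence in Statistical Analysis is shorthand spanning both substudies, and the handling of individual losses can be left to a fuller document.

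Much of this stands. A reader might infer that control losses cannot be counted at all, so that the control risk is zero by construction. With 300 per group, six exposed losses against none gives a two-sided Fisher P of .030. If the true risk were equal in both groups, the chance of six or more exposed losses would be 8% at a loss risk of 1% and over 99% at 5%. The documents do not support treating those figures as the plan's error rate. They require every exposed loss to be kept, every control loss to be dropped, and loss risks that the article does not give.

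A reader might also infer that BORN must fall short by the number of losses. That does not follow either, because Study Design admits neonates of eligible mothers who did not take part in PREGNANT.

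The reply does not remove the conflict. Two sections give different control populations for the same comparison, and the one in the analysis section is the one that can remove the outcome. The postpartum serology condition adds a second route by which control losses can drop out. A contradiction between stated rules is not a detail left to another document.

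**Conclusion.** The point holds as an inconsistency with a possible bias, not as a demonstrated one. The article gives two control definitions for PREGNANT, makes control status depend on a postpartum test while exposure is settled in pregnancy, and does not classify a control pregnancy that ends in loss. Depending on the reading, the relative risks for abortion and fetal death are unbiased, undefined or too high.

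The size cannot be derived from the documents. With a true relative risk of 1, all exposed losses counted and half of the control losses omitted, the observed value is 1.85 to 1.98 over assumed loss risks of 15% down to 2%. This illustrates the sensitivity and does not estimate what will happen. Outcomes measured only in live-born children are not affected by this argument. The point should be settled before analysis.

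**What to change.** 1. In Statistical Analysis, align the PREGNANT control group with Study Design: all enrolled nonexposed pregnancies, whatever their outcome. Count abortions and fetal deaths in numerator and denominator in both groups.
2. State how nonexposure is confirmed after a pregnancy loss, including when serology is taken and how women without that test are handled, so that such controls are not dropped.
3. Use mother-child dyads or live-born children as the unit only for neonatal and BORN outcomes, and use the word dyad in one sense throughout.
4. At most, note in Sample Size Calculation that 300 exposed women do not by themselves guarantee 300 exposed children. No loss-adjusted formula is needed, since BORN can also take neonates of eligible non-participating mothers.

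The cost is rewording, and keeping the records of control pregnancies without a child in the PREGNANT data set. No larger sample is needed. The article says that analysis will start only after data collection, so the change can still be made in advance.

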**Methods:**

The PROUDEST trial comprises 2 prospective, sequential substudies. The *PREGNANT* substudy will clinically assess the effects of SARS-CoV-2 infection on pregnancy, childbirth, and puerperium from a mechanistic standpoint to elucidate the pregnancy-related inflammatory and immunological phenomena underlying COVID-19. Pregnant women aged 18-40 years who have been exposed (proven with laboratory tests) to SARS-CoV-2 (group A; n=300) will be compared to control subjects with no laboratory evidence of in-pregnancy exposure to the virus (group B; n=300). Subjects exposed to other infections during pregnancy will be excluded. The *BORN* substudy is a long-term follow-up study that will assess the offspring of women who enrolled in the prior substudy. It will describe the effects of SARS-CoV-2 exposure during pregnancy on children’s growth, neurodevelopment, and metabolism from birth up to 5 years of age. It includes two comparison groups; group A (exposed; n=300) comprises children born from SARS-CoV-2–exposed pregnancies, and group B (controls; n=300) comprises children born from nonexposed mothers.

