**Figure 2 figure2:**
[figure not shown]
PROUDEST study design. CNS: central nervous system; MRI: magnetic resonance imaging; PROUDEST: Pregnancy Outcomes and Child Development Effects of SARS-CoV-2 Infection Study.

Prenatal data from both the pregnant women and their fetuses will be gathered during the follow-up at the Pregnancy Outpatient Clinic of the University Hospital of Brasilia. These data will consist of the medical and sociodemographic data of the mothers; gestational age; symptoms, interventions, and outcomes related to COVID-19 (for SARS-CoV-2–exposed participants); congenital infection screening results; hypertensive disorders and other pregnancy-specific morbidities; general health assessments; general physical examinations; routine clinical biochemistry tests; and ultrasound scans. These scans will be performed between gestational weeks 11-13 and gestational day 6, from gestational week 22 to gestational week 24, and on a monthly basis in the third trimester of pregnancy to assess fetal growth and morphology, placental morphology, amniotic fluid volume, and dopplerfluxometry results. Maternal blood will be collected at the first prenatal consultation, regardless of gestational age. Antenatal consultations will occur monthly up to week 34, every 2 weeks between weeks 34 and 36, and then weekly up to delivery. During pregnancy, psychological risk assessments and mental health screens will be performed with the Beck Depression Inventory during the first prenatal consultation. [40]. Individual psychological care will be provided to pregnant women who have a Beck Depression Inventory score of >12. Mothers will also be physically and psychologically evaluated between days 7 and 21 postpartum during the PREGNANT substudy and after the BORN substudy.

At childbirth, assessments will be conducted to identify the occurrence of dysfunctional labor and the premature rupture of membranes, the type of birth, and delivery outcomes. We will also conduct physical examinations and classifications of the newborns and anthropometry. The early initiation of breastfeeding, the need for neonatal intensive care, and the type of interventions will also be identified. Maternal blood, CSF from women undergoing spinal anesthesia for a cesarean section, and umbilical cord blood samples will be collected.

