CSF will be collected immediately before the infusion of the medicine for spinal anesthesia, which will be injected via a sterile syringe at an average dosage of 0.5 ml. CSF will be collected in a 4-mL cryotube. Blood samples from mothers and the umbilical cord will be collected in a heparinized tube and centrifuged immediately, and the plasma will be stored in 4-mL sealed cryotubes. CSF and blood samples will be subsequently stored at −80 °C for later analysis. The assessment of blood cell counts, inflammation markers (C-reactive protein and procalcitonin), biochemistry (alanine aminotransferase, aspartate aminotransferase, ferritin, alkaline phosphatase, and lactic dehydrogenase) and SARS-CoV-2 tests (RT-PCR and IgM and IgG antibody tests) will be carried out.

Circulating cytokine levels will be evaluated with the Luminex Bio-Plex Pro Human Cytokine 27 platform (Bio-Rad Laboratories). The cytokine profile assessment will analyze chemokines (CXC motif chemokine ligand [CXCL] 8, CC motif chemokine ligand [CCL] 11, CCL3, CCL4, CCL2, CCL5, and CXCL10), proinflammatory cytokines (interleukin [IL]-1β, IL-6, tumor necrosis factor, IL-12p70, interferon γ, IL-17A, and IL-15), regulatory cytokines (IL-1Ra, IL-4, IL-5, IL-9, IL-10, and IL-13), and cell growth factors (IL-2, IL-7, basic fibroblast growth factor, platelet-derived growth factor, vascular endothelial growth factor, granulocyte colony-stimulating factor, and granulocyte-macrophage colony-stimulating factor). All procedures will be performed according to the manufacturer's recommendations.

Analyses will be performed at the clinical biochemistry laboratories of the hospitals where delivery occurred (blood cell count, C-reactive protein, procalcitonin, and routine biochemistry assessments), the Central Laboratory of the Federal District Department of Health (Laboratório Central de Saúde Pública; SARS-CoV-2 tests), and the University of Brasilia laboratory (cytokine profile assessments).

The placenta will be subjected to fresh histopathological analyses for assessing possible morphological and histological changes that may be associated with SARS-CoV2 infection. Histopathological analysis will be conducted according to the Amsterdam protocol [41].

Peripheral blood and CSF samples from the newborns will only be collected if there is clinical need; this will not be done per the routine research protocol. If such specimens are made available, they will also be subjected to the aforementioned analyses.

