## Discussion

### Study Implications

The PROUDEST offers comprehensive insight (from both the obstetric and pediatric perspectives) into the effects of SARS-CoV-2 infection on the global health of pregnant women and their offspring. Specifically, the study will fill the deep gap in knowledge about the consequences of SARS-CoV-2 infection during early gestation (ie, the period when the critical stages of embryogenesis take place), as women in all stages of pregnancy will be followed. The virus-induced inflammatory and immunological phenomena that occur in SARS-CoV-2–exposed mothers during this early period of life may have a particular impact on placental and fetal physiology or may even be associated with epigenetic signals. Therefore, these phenomena could conceivably affect the long-term outcomes of a child’s growth, development, and metabolism.

A better understanding of these potential long-term consequences requires lengthy, prospective observational studies, such as the PROUDEST. This study will not only address the clinical outcomes associated with in-pregnancy exposure to COVID-19 but also evaluate a host of soluble tissue biomarkers (as described in this protocol) with the aim of comprehensively understanding the mechanisms underlying related clinical phenomena.

Our data will add to the overall clinical and basic knowledge base for COVID-19, and our ultimate goal is to provide grounds for better managing SARS-CoV-2–exposed pregnant women and their children through direct means or by setting the stage for additional studies. In fact, the PROUDEST opens up a broad spectrum of possibilities for further, multidisciplinary research on the effects of SARS-CoV-2 infection on maternal, fetal, and pediatric health. Furthermore, our results might prove to be relevant from a social perspective, as they may provide data that support the tailored development and implementation of health policies that are specifically oriented to this particular demographic group.

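### The working definition of a control is looser than the abstract's, so some women infected in pregnancy can enter group B

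*Protocol article*

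**What the plan says.** **Abstract (Methods).** Group B is made up of "control subjects with no laboratory evidence of in-pregnancy exposure to the virus".

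**Study Design.** A woman counts as exposed on a positive RT-PCR, serology or "rapid test that returns positive results during pregnancy and is confirmed by a second test". For the other group, "Nonexposure to COVID-19 will be defined as asymptomatic pregnant women with negative serology tests", and the timing of that serology is given as "which will be conducted at 14-21 days postpartum".

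**Statistical Analysis.** Controls are nonexposed dyads that meet the inclusion criteria, with one further sentence: "those with positive serology tests (IgG and IgM tests conducted at 14-21 days postpartum) will not be included in the control group".

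**Procedures.** "Maternal blood will be collected at the first prenatal consultation, regardless of gestational age", and again at childbirth. After describing the handling of the blood and CSF samples, the section says that "SARS-CoV-2 tests (RT-PCR and IgM and IgG antibody tests) will be carried out". No sentence links these results to membership of the control group.

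**Elsewhere.** Children in BORN are grouped by their mother's exposure status (Study Design). The Discussion says that "the study will fill the deep gap in knowledge about the consequences of SARS-CoV-2 infection during early gestation", and aim 8 compares exposure at different stages of pregnancy.

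**The concern.** The exposed and nonexposed definitions do not complement each other, and the working rule for controls does not deliver what the abstract describes. Two kinds of woman can pass it.

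1. A symptom-free woman with one positive test in pregnancy that no second test confirmed. She is not exposed under Study Design. If she is seronegative 14-21 days after birth, she meets every stated condition for a control. Yet she has laboratory evidence of the kind that the abstract rules out.
2. A woman with a silent infection early in pregnancy whose antibodies are no longer detectable after birth.

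Infected women in group B raise the risk in the comparison group and pull contrasts toward no effect. Because BORN inherits the mother's status, the error would last through five years of child follow-up. The plan's remedy for group differences is covariate adjustment, which does not correct a wrong exposure label.

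**Working it through.** **The definitions side by side.** Take a symptom-free woman with one unconfirmed positive RT-PCR in pregnancy and negative IgG/IgM at 14-21 days postpartum.

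- Abstract: she has laboratory evidence of exposure, so she is not a control.
- Study Design, exposed: no second test confirms the result, so she is not exposed.
- Study Design, nonexposed: no symptoms and negative postpartum serology, so she is nonexposed.
- Statistical Analysis: no positive postpartum serology, so she is not removed.

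The conflict follows from the text alone.

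**The gap for early infection.** From week 8 to delivery at 39-40 weeks is 31-32 weeks. Adding 2-3 weeks to the postpartum serology gives 33-35 weeks between infection and the only test that the control rule names.

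**Size.** The plan states no misclassification rate, so there is no figure of its own to reproduce. Inputs:

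- p, share of pregnancies infected: 15% (Sample Size Calculation), with 30% as an assumed upper value
- a, share of infections without symptoms: 50% (assumed)
- m, share of infected women seronegative at 14-21 days postpartum: 10-30% (assumed)

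The misclassified share of controls is c = p·a·m / [(1 − p) + p·a·m]. If misclassified women carry the same risk as group A, the observed relative risk is RR / [1 + c(RR − 1)]. For RR = 2 this is 2 / (1 + c), whatever the baseline risk.

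| p | m | c | of 300 | true 2.0 seen as |
|---|---|---|---|---|
| 0.15 | 0.10 | 0.0075 / 0.8575 = 0.9% | 3 | 1.98 |
| 0.15 | 0.30 | 0.0225 / 0.8725 = 2.6% | 8 | 1.95 |
| 0.30 | 0.10 | 0.0150 / 0.7150 = 2.1% | 6 | 1.96 |
| 0.30 | 0.30 | 0.0450 / 0.7450 = 6.0% | 18 | 1.89 |

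**Power.** With 300 per group, two-sided 5%, an assumed 10% risk in controls and a true relative risk of 2.0, power is 93.1% with no misclassification. It is 92.6% at c = 0.9% and 89.0% at c = 6.6%, which lies slightly beyond the top of the range.

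**What the formula covers.** It counts every infected, symptom-free, seronegative woman. A truly infected woman with an unconfirmed positive is therefore already included, and a false positive is not misclassified. The formula also counts women whose positive was confirmed in pregnancy. They belong to group A, so on that score the range is somewhat too high.

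**The case against.** Much of the case for leaving the rule alone is sound, and it limits what can be claimed.

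- A reader might infer that nonexposure rests on one postpartum serology and that tests in pregnancy are ignored. The text does not support this. Controls must also be without symptoms, and a confirmed positive in pregnancy places a woman in group A. The Statistical Analysis sentence can be read as an added exclusion rather than the whole rule. This stands, but it does not close the gap, because the nonexposed definition to which that sentence would be added is itself only the absence of symptoms plus postpartum serology.
- An unconfirmed positive in a symptom-free woman who is later seronegative may be a false positive. This stands: such women are of uncertain status and should not be counted as infected.
- SARS-CoV-2 testing of the first-consultation blood is not explicit. The list of tests follows the account of childbirth sampling and fits that time most naturally. This stands, so first-visit results cannot be assumed to exist.
- The childbirth sample precedes the postpartum serology by only 2-3 weeks. An early infection missed by one serology will usually be missed by the other. This also stands.
- A condensed article may leave indeterminate tests to a fuller document. That would excuse silence. Here, however, the article states two rules for its central variable, and they classify the same woman differently.
- The study calls itself exploratory and the bias is small. That bears on the priority of the point, not on whether the definitions should agree.

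**Conclusion.** The point holds as a conflict between definitions with a modest likely effect. The control rule in Study Design and Statistical Analysis is looser than the abstract's. Women with a single unconfirmed positive, or with a silent early infection that serology no longer shows, can enter group B; the documents do not show that any do.

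Under the stated assumptions 0.9-6.0% of controls would be misclassified, and a true relative risk of 2.0 would be seen as about 1.98-1.89. Only the 15% prevalence comes from the documents. A reader might arrive at 1.97-1.80 by setting the symptom-free share to 1 (c = 0.015 / 0.865 = 1.7% to 0.09 / 0.79 = 11.4%). That drops a condition which Study Design imposes, so it is not the right range.

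The effect could be larger for early-gestation infection, which the study particularly wants to clarify, but only if antibodies wane over the long gap to the test. The documents give no data on this.

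**What to change.** Reconcile Study Design and Statistical Analysis with the abstract before groups are fixed for analysis:

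- Require controls to be negative on every SARS-CoV-2 result available from the pregnancy (the childbirth sample, the first-consultation sample where it was tested, and the surveillance record used for recruitment) as well as on the postpartum serology, and keep the no-symptoms condition.
- Put women with a single unconfirmed positive in neither group for the main analysis. As a sensitivity analysis, place them in group A and then in group B.
- Apply the same assignment to their children in BORN.
- State the remaining misclassification as a limitation, since the childbirth sample adds little for early infections that have already become seronegative.

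The cost is a few sentences and the use of results already available. A few controls would be set aside. Both the abstract and the Results section schedule analysis for after data collection is complete, so the rule can be settled first.
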